### Assessments and Survey Measures

Participants completed online surveys at baseline and at 3, 6, 9, 12, 15, and 18 months (Figure 2). Comprehensive surveys, lasting approximately 30 minutes, were administered at baseline, 3, 6, 12, and 18 months. The 6-month survey also included an assessment of the intervention program completed after intervention delivery. Short surveys, focused on PrEP uptake and adherence and lasting about 15 minutes, were administered at 9 and 15 months. All surveys were hosted on REDCap, a HIPAA-compliant platform.

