**Figure 2 figure2:**
[figure not shown]
Study schema and flow diagram. DBS: dried blood spot; LS4M: LifeSkills for Men; PrEP4T: PrEP for transgender men and transmasculine people.

Survey measures were guided by the Healthcare Accessibility [49], Gender Affirmation [7,51], and IMB [53] frameworks. Validated measures from transgender populations and prior research were selected to ensure comparability [59-62]. Baseline surveys included both lifetime and past 3-month recall, while follow-up surveys assessed past 3-month recall only. Domains assessed included demographics (age, race, ethnicity, gender identity, sexual orientation, education, income, housing, health insurance), gender affirmation (social, medical, legal), and unmet gender affirmation needs [59,61]. Measures included the PrEP cascade (awareness, indications, uptake, adherence, and persistence, including both daily oral and long-acting injectable formulations) [15,62]; barriers and facilitators to PrEP care [8,62]; PrEP knowledge, motivations, and preferences [8,15,63]; PrEP self-efficacy [64]; and PrEP empowerment [65]. Behavioral risk for HIV acquisition was assessed through sexual partners and practices using an adaptation of the Transmasculine Sexual Health Assessment [66], as well as injection drug use, needle-sharing behaviors, and perceived HIV risk [62]. Sexual partner communication and affirmation were measured using the Sexual Communication Self-Efficacy Scale [67] and the Gender Non-Affirmation from Sexual Partners Scale [14], respectively. Additional questions addressed HIV testing outside the study and sexually transmitted infection screening and diagnoses [61]. Mental health measures included psychological distress (Kessler-6) [68], posttraumatic stress disorder symptoms (Primary Care Posttraumatic Stress Disorder Screen) [69], resilience (Brief Resilience Scale) [70], and use of mental health services (eg, psychotherapy, support groups). Alcohol use disorder was assessed with the Alcohol Use Disorders Identification Test—Consumption [71], substance use disorder symptoms with the Drug Use Disorder Identification Test—Consumption [72], along with categories of drugs used. Discrimination was measured using the Everyday Discrimination Scale [73], which included 14 possible attributions (eg, age, gender identity, race, ethnicity). Internalized stigma [61] was also assessed. Additional measures included health care empowerment [74], health care access, utilization, and mistreatment in health care settings [60]. Social support was assessed with a short form of the Social Support Questionnaire [75], the Trans Community Connectedness subscale of the Gender Minority Stress and Resilience Measure [76], and metrics of social network size [61].

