#### Condition D (SOC + PrEP4T + LS4TM)

This is an online peer-delivered combined intervention. Participants in this arm received both PrEP4*t* (1-on-1) and LS4TM (group-based) interventions in addition to SOC. Group D received a total of 21 hours of content, consisting of six 2-hour LS4TM sessions and six 1.5-hour PrEP4T sessions. These interventions were not delivered simultaneously within the same 6-week period.

**Table 2 table2:** PrEP4T^a^ intervention sessions: session number, title, content, and conceptual framework guiding the intervention sessions.

Session number	Session title	Session content	Conceptual framework
1	Introduction, Background, and Goal Setting	Build rapport with the participant Assess the participant’s background and sexual health history. Set a realistic, sexual health–related goal for the program (eg, to start PrEP^b^, to consistently communicate with partners about sexually transmitted infection testing). Discuss factors that may impact risk for HIV among transgender men and transmasculine people.	IMB^c^ and Gender Affirmation
2	HIV Transmission and Prevention	Assess what participants know about HIV prevention and how they currently put that information into practice. Introduce participants to the concept of harm reduction. Fill in knowledge gaps and answer questions about HIV prevention. Build on or reinforce participants’ existing harm reduction strategies.	IMB and Healthcare Accessibility
3	Accessing PrEP and Preventive Health Care	Discuss barriers to accessing PrEP and work with participants to identify solutions and options available to them. Provide a brief overview of where and how participants can access postexposure prophylaxis. Discuss preventive health care access, with an emphasis on primary care and sexually transmitted infection testing. Address other preventive care topics, including vaccinations (human papillomavirus, hepatitis A and B), contraception, cervical and anal Papanicolaou testing, and gender-affirming care.	IMB and Gender Affirmation Healthcare Accessibility

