Aim 2 will use causal inference methods from epidemiology [96,97] to conduct mediation analyses and examine the mechanisms of action for the interventions. Mediation analyses will estimate the natural direct and indirect effects of proposed mediators—health care empowerment, TMSM community connectedness, and IMB constructs—on the relationship between intervention condition and PrEP uptake compared with SOC. Mediation models will be implemented using a series of random-effects logistic regression models, consistent with the approach described in aim 1.

For aims 1 and 2, patterns of missingness will be examined, and baseline responses will be compared between participants with and without missing data. Variables associated with missingness will be included in the analyses to yield valid inferences [98]. Modern missing data techniques [99] will be employed, with multiple imputation used to handle missing data, including participants lost to follow-up [100]. Sensitivity analyses will compare parameter estimates from completer-only analyses with those from multiple imputation to assess potential bias.

Aim 3 qualitative data from IDIs will be analyzed to explore PrEP decision-making and participant experiences with the interventions. An iterative analytic process will follow Crabtree and Miller’s [101] 5-step approach: (1) describing, (2) organizing, (3) connecting, (4) corroborating, and (5) representing. Regular debriefing meetings with data collectors will identify preliminary findings and guide iterative data collection and analysis. An initial set of codes will be developed based on the study’s conceptual frameworks of Healthcare Access, Gender Affirmation, and IMB constructs. Qualitative codes will be applied to transcripts and interview notes using qualitative analysis software by 2 independent analysts. New codes will be added as themes emerge. Summaries will be created for major themes and differences across subgroups. Descriptive quantitative survey data (eg, demographics, social and medical gender affirmation) may be used to contextualize qualitative findings. CAB members will provide ongoing input and help corroborate the qualitative results.

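### Aim 2 names only random-effects logistic models for mediators that are scale scores, and its Aim 1 visit template omits the one survey that precedes the first follow-up DBS

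*Protocol article*

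**What the plan says.** All of this is in the protocol article.

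- **Framework and estimand (Data Analysis by Aim).** "Aim 2 will use causal inference methods from epidemiology [96,97] to conduct mediation analyses", and "Mediation analyses will estimate the natural direct and indirect effects of proposed mediators". No effect scale is given.
- **Models (same section).** "Mediation models will be implemented using a series of random-effects logistic regression models, consistent with the approach described in aim 1". No other model family is named for any part of the mediation work.
- **Mediators (Assessments and Survey Measures).** These are survey instruments. Community connectedness, for example, is "the Trans Community Connectedness subscale of the Gender Minority Stress and Resilience Measure [76". The IMB constructs include "PrEP knowledge, motivations, and preferences [8,15,63]; PrEP self-efficacy [64]; and PrEP empowerment [65". No cut-point is given for any of them.
- **Timing of mediators (Assessments and Survey Measures).** "Comprehensive surveys, lasting approximately 30 minutes, were administered at baseline, 3, 6, 12, and 18 months".
- **Timing of the outcome.** DBS kits are collected at baseline, 6 and 12 months (HIV Testing, Biomarker-Confirmed PrEP Outcomes, and Specimen Collection Protocol). The Aim 1 model uses baseline, 6, 12 and 18 months.
- **Condition D.** Its two courses are sequential: "These interventions were not delivered simultaneously within the same 6-week period".

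**The concern.** A natural indirect effect needs a model for the mediator as well as one for the outcome. Logistic regression suits uptake, which is yes/no. It does not suit a score, so an analyst following the sentence literally must misfit the score or invent a cut-point. A cut-point discards information and adds an unplanned choice.

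Two further matters are left open.

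1. **Scale.** For an outcome that is not rare, the conditional log-odds ratio for treatment moves when any predictor of the outcome is added, whether or not that predictor mediates. If indirect effects were read from changes in logistic coefficients, this shift would be counted as mediation, or would mask it.
2. **Order.** The only visit template Aim 2 points to is Aim 1's, and month 3 is not in it. Yet the 3-month survey is the only post-baseline survey that comes before the first follow-up DBS. If mediator and uptake come from the same visit, starting PrEP may itself have raised PrEP knowledge, self-efficacy and empowerment.

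Hypothesis 2.1 is the sole hypothesis of Aim 2, so these choices bear directly on what can be said about mechanism. They do not touch the primary between-arm comparison.

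**Working it through.** Aim 2 states no figure to reproduce. The adjacent enrolment figure does reproduce: 300/(1 − 0.20) = 375. The article gives no SOC uptake, mediator SD or mediator effect, so every input below marked *assumed* is only that.

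**1. Is uptake a common outcome?** The Power section gives a 20% increase, 75 per condition and at least 80% power at .05, without saying whether the increase is absolute or relative.

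- As 20 points, with 75 per arm and a two-sided test, power is 0.94, 0.87, 0.81, 0.77 and 0.71 at SOC rates of 5, 10, 15, 20 and 30%.
- As a relative 20%, power is only about 0.05 to 0.29 over SOC rates of 5 to 40%, even with 150 per factor level.

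So the increase reads as absolute, and uptake in the intervention arms would be at least 20%. An SOC rate above 40% would make uptake common in any case.

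**2. Coefficient shift with no mediation** (*assumed*: mediator M standard normal and unaffected by arm; log-odds b per SD). For each arm with marginal risk p, solve E[expit(c + bM)] = p for c. The conditional log-OR is c₁ − c₀, the marginal log-OR is logit(p₁) − logit(p₀), and apparent mediation is (marginal − conditional)/marginal. For 20% versus 40% the marginal log-OR is −0.405 + 1.386 = 0.981.

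| b (OR per SD) | conditional log-OR, 20% v 40% | apparent mediation, 20% v 40% | 15% v 35% | 30% v 50% |
|---|---|---|---|---|
| 0.5 (1.65) | 1.029 | −5% | −4% | −6% |
| 1.0 (2.72) | 1.160 | −18% | −17% | −20% |
| 1.5 (4.48) | 1.344 | −37% | −34% | −40% |

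The truth is 0 throughout.

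**3. The same problem with real mediation** (*assumed*: control uptake 15%, arm effect on the mediator 0.5 SD, b = 1.0, direct log-OR 0.8). Write R(x, m) for the risk with treatment at x and the mediator distributed as under m. Then R(0,0) = 0.150, R(1,0) = 0.261 and R(1,1) = 0.350.

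- Natural indirect effect: 0.350 − 0.261 = 0.089 of a total 0.350 − 0.150 = 0.200, or 44% on the risk scale.
- On the log-odds scale it is 0.42 of 1.11, or 38%.
- Differencing coefficients gives 0.31 of 1.11, or 28%.
- Multiplying coefficients gives 0.50 against the true 0.42.

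The mediation formula recovers the truth, but the answer still depends on the scale, so the scale has to be named. Random intercepts widen the gap: the ratio of marginal to conditional log-OR is about 0.86, 0.65 and 0.49 at intercept SDs of 1, 2 and 3.

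**4. Same-visit feedback** (*assumed*: M = d·Y + standard normal noise, with no effect of M on uptake Y; risks 20% and 40%). The arm effect on M is d(0.40 − 0.20) = 0.2d, and the log-odds slope of Y on M is d. For d = 0.3, 0.5 and 0.8 the false indirect risk difference is 0.004, 0.011 and 0.027 of 0.200, or 2%, 6% and 14%. At 15% versus 35% it is 2%, 5% and 13%. In the same set-up a mediator measured before uptake gives 0.

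**5. Why not pair the 6-month mediator with the 12-month DBS and adjust for 6-month PrEP status?** That status is affected by randomization and may also affect the mediator, so standard g-computation no longer identifies natural effects. The adjustment also blocks the route through early uptake. A simulation of 400,000 records (*assumed*: early mediator effect 0.5 SD, log-odds 1.0 per SD on 6-month uptake, 3.0 from 6- to 12-month use) had a true indirect effect of 0.05 to 0.07. The adjusted analysis returned 0.00 to 0.02.

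**The case against.** A reader might infer that the planned indirect effects will be distorted and that mediator and outcome are taken at the same visit. The article supports neither. It commits to natural effects by causal methods, and a logistic outcome model used in the mediation formula does not carry the coefficient-shift problem. The article nowhere proposes differencing or multiplying coefficients. It pairs no mediator visit with any outcome visit, and it neither assigns nor excludes the 3-month survey. Lagging and effect scale are details that a condensed article may leave to a fuller plan. The feedback bias is small to modest, and the larger scale shifts need a strong mediator. All of that stands, and it limits the point.

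It can also be argued that the sentence on logistic models describes only the models for the binary outcome, and that the plan undertakes to check variable distributions against model assumptions. This stands only in part. The sentence speaks of the mediation models as a series and names one family. A distribution check does not say what replaces an unsuitable model. The model choice is a positive statement in this document, not an omission.

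**Conclusion.** The point holds in limited form. The article fixes one model family for the whole mediation series, and that family does not suit scale-score mediators without an unstated cut-point. It models the series on Aim 1, whose visits omit the survey best placed to come before the first follow-up DBS.

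The consequences for the indirect effects are conditional. If log-odds coefficients are compared, the shift runs from a few percent to over a third of the total effect. If mediator and outcome share a visit, about 2% to 14% of the effect can be spuriously mediated. These sizes rest on assumed uptake, mediator strength and feedback. That uptake is common is inferred from the power statement. Neither distortion is established as part of the plan.

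**What to change.** Replace the sentence on the mediation models with the following specification:

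- linear models for the scale mediators and a logistic model for biomarker-confirmed uptake;
- natural direct and indirect effects by the mediation formula (g-computation) on the risk-difference scale, with bootstrap confidence intervals;
- the mediator from the 3-month survey and the outcome from the 6-month DBS, adjusted for the baseline mediator and baseline PrEP status;
- no adjustment for 6-month PrEP status, which is a post-randomization outcome;
- results with and without condition D.

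With one mediator visit and one outcome visit per person, no participant-level random intercept is needed.

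**Cost.** Some extra programming on data the schedule already collects. Fewer visits are used, so precision is somewhat lower. Two sequential 6-week courses take at least 12 weeks, so some condition D participants may not have finished both by month 3, hence the two sets of results. PrEP started before the 3-month survey can still feed back on the mediator, so the earlier visit reduces reverse causation but does not remove it. The report should say so.

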#### Data Analysis by Aim

We describe the planned analyses by aim.

Before analyses, data will be audited for quality and completeness. Descriptive statistics will be calculated, and variable distributions will be evaluated to ensure they meet the assumptions of planned analytic models, including detection of outliers. In this study, *t* tests and chi-square analyses will be used to assess group equivalence at baseline. Variables showing differences across the 4 groups will be considered for inclusion as covariates in the analyses. All analyses will be conducted using SAS (SAS Institute) or R (R Foundation) software, with statistical significance set at an α level of .05.

Aim 1 analyses will follow an intention-to-treat approach. Random-effects logistic regression will be used with PrEP uptake as the primary outcome. The model will include time (baseline, 6, 12, and 18 months), a categorical variable for study condition (PrEP4T, LS4TM, PrEP4T + LS4TM, with SOC as the reference), and the time × study condition interaction to test whether changes in PrEP uptake over time differ across the 3 intervention conditions compared with SOC. Baseline characteristics that differ across study conditions, as well as variables related to missingness, will be included as covariates if necessary. The primary parameter of interest is the time × study condition interaction term; a significant interaction would indicate that the rate of PrEP uptake over time differs between the intervention and SOC groups. Significant interactions will be graphed and interpreted. We hypothesize that PrEP uptake will be highest among participants randomized to condition D (PrEP4T + LS4TM). The same analytic approach will be applied to the secondary outcome of PrEP adherence. PrEP persistence will be assessed at months 12 and 18 using random-effects logistic regression, including time (12 and 18 months), study condition, and the time × study condition interaction. HIV and sexually transmitted infection incidence will be evaluated using logistic regression, with incidence between baseline and 18 months as the outcome and study condition as the predictor.

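### The only covariate criteria stated for the mediation analysis (arm imbalance and missingness) do not target mediator-outcome confounding, on which the Aim 2 indirect effects depend

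*Protocol article*

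**What the plan says.** All of the following is in the Data Analysis by Aim section of the protocol article unless noted.

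- **Aim 2 framework and target.** "Aim 2 will use causal inference methods from epidemiology [96,97] to conduct mediation analyses", and "Mediation analyses will estimate the natural direct and indirect effects of proposed mediators". The mediators are health care empowerment, community connectedness and the information, motivation and behavioral skills constructs. Each is assessed against SOC.
- **Aim 2 model.** "Mediation models will be implemented using a series of random-effects logistic regression models, consistent with the approach described in aim 1".
- **Covariates, general.** Before any aim is discussed: "Variables showing differences across the 4 groups will be considered for inclusion as covariates in the analyses".
- **Covariates, Aim 1.** "Baseline characteristics that differ across study conditions, as well as variables related to missingness, will be included as covariates if necessary".
- **Covariates, Aims 1 and 2 together.** In the missing-data paragraph: "Variables associated with missingness will be included in the analyses to yield valid inferences [98". The one sensitivity analysis named there compares completers with multiple imputation.

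No sentence selects a covariate because it affects both a mediator and uptake, and none states the assumption of no mediator-outcome confounding.

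On data, the Assessments and Survey Measures section says "Comprehensive surveys, lasting approximately 30 minutes, were administered at baseline, 3, 6, 12, and 18 months". The domains listed there cover the mediators and the PrEP cascade. A dried blood spot (DBS) sample is also taken at baseline.

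**The concern.** Randomization makes condition independent of baseline characteristics, so the effect of condition on the mediator and its effect on uptake are both protected. The effect of the mediator on uptake is not, because nobody is randomized to a level of empowerment or self-efficacy. A natural indirect effect is built from the first and third of these links, so it needs the common causes of mediator and uptake to be controlled.

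Whether a baseline variable differs between arms says nothing about whether it is such a common cause. A participant who already uses PrEP, or starts with high self-efficacy, may well score higher on the mediator later and also be on PrEP later. The variables behind this are balanced across arms by design, and so tend to be passed over by a test that looks for imbalance.

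At stake is Hypothesis 2.1. If a program raises a mediator that does nothing, pre-existing differences between participants can make that mediator look like the route to uptake, and it could be carried into scale-up as a mechanism.

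**Working it through.** The article gives no figure for Aim 2, so there is none to reproduce. The check asks how often the stated criteria would admit a true confounder, and what follows if they do not.

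**Inputs from the article.** Four conditions, 75 per condition (Table 1 and the Power section); significance level .05, taken as two-sided.

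**Assumed inputs.** Uptake is about 20% in SOC and 40% in each active arm. Each program shifts the mediator M by a = 0.5 SD (also 0.3). A baseline factor U correlates c with M within arms and has log odds ratio d per SD on uptake. M itself has no effect on uptake.

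**Step 1: entry by imbalance.** U is balanced by randomization, so a test at .05 flags it with probability 0.05 and misses it with probability 1 − 0.05 = 0.95, whatever c and d are. In the simulations it entered in 4% to 6% of trials.

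**Step 2: spurious mediator effect.** With U omitted, the log odds ratio for M is about d × cov(M, U)/var(M) = c × d, because the within-arm variance of M is 1. For c = 0.5 and d = 0.5 this is 0.25, an odds ratio of exp(0.25) = 1.28 where the truth is 1. For stronger confounding the logistic model shrinks this somewhat.

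**Step 3: how often mediation is declared.** The indirect effect of the combined arm versus SOC counts as declared when both paths have P<.05. Single-visit logistic outcome model, a = 0.5, 2000 runs per row. The stated-criterion column adjusts for U only if it differs across the four arms at P<.05.

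| c | Odds ratio per SD of U | exp(c × d) | Simulated median odds ratio for M | Declared, imbalance criterion | Declared, U always adjusted |
|---|---|---|---|---|---|
| 0 | 1.00 | 1.00 | 0.99 | 4.0% | 4.1% |
| 0.3 | 1.35 | 1.09 | 1.10 | 8.7% | 5.0% |
| 0.3 | 1.65 | 1.16 | 1.15 | 17.5% | 5.1% |
| 0.5 | 1.65 | 1.28 | 1.27 | 41.1% | 5.9% |
| 0.5 | 2.23 | 1.49 | 1.43 | 66.9% | 4.5% |
| 0.6 | 2.72 | 1.82 | 1.70 | 80.2% | 5.1% |

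With a = 0.3 the declared rates in the same order are 1.9%, 5.6%, 9.2%, 21.8%, 36.5% and 42.5%, against 1.8% to 4.0% when U is always adjusted for. A Sobel test is more conservative: 2.7% to 70.4% over the five confounded rows at a = 0.5.

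**Step 4: does the random intercept help?** The simulation was repeated with a random-intercept logistic model over three visits (300 runs per setting, a = 0.5). The rate was 4.0% without confounding, 18.0% at c = 0.3, d = 0.5, and 69.0% at c = 0.5, d = 0.8. With U adjusted for, it was 4.0% to 6.3%. The random intercept is assumed independent of the mediator, so it does not absorb the confounding.

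**Step 5: a concrete confounder.** The listed inclusion criteria do not exclude current PrEP users. Suppose 10% to 30% of entrants use PrEP at baseline, score 0.5 to 1 SD higher on the mediator at follow-up, and have 85% later uptake, against 15% (SOC) or 35% (program) in the others. With the imbalance test applied (600 runs per setting), the false indirect effect is 1.6 to 5.1 percentage points and is declared in 10% to 63% of trials. With baseline PrEP always in the model, it is about 0 points and 3% to 5%.

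The missingness route was not simulated. To the extent that it admits a confounder, the unadjusted rates above are too high.

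**The case against.** A reader might infer that Aim 2 formally inherits the Aim 1 covariate rule and that this rule shuts confounders out. The text does not go that far. The wording that ties Aim 2 to Aim 1 may refer only to the type of model, and Aim 2 opens with its own framework by citing causal inference methods. The criteria are permissive: variables are to be considered, or added if needed, and nothing says that no others may enter. Some confounders, such as insurance or health care access, could come in as predictors of missingness, particularly with about 20% loss anticipated. The cited methods or an analysis plan that is not shown may supply an adjustment set, and a journal article need not list covariates.

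These points stand, and they limit the claim to what happens if the stated criteria are used alone. They do not remove it. The imbalance criterion is also stated for the analyses in general, so the point does not hang on how the link to Aim 1 is read. A stated selection criterion that is unrelated to the estimand is also different from a list left for later. Admission through missingness depends on who drops out, not on what confounds.

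**Conclusion.** The stated covariate criteria are not aimed at mediator-outcome confounding, and the Aim 2 indirect effects require that confounding to be controlled. If they are used alone, an inert mediator that a program moves can be declared a mechanism more often than the nominal rate. At the planned size and a 0.5 SD shift, the rate is near nominal under weak confounding (about 9%, against 4% with none) and roughly 20% to 70% under moderate to strong confounding. It is about half that with a 0.3 SD shift.

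These sizes rest on assumed confounding strengths, on a program that truly moves the mediator, and on the confounder not entering as a predictor of missingness. The documents therefore do not support the stronger conclusion that Hypothesis 2.1 would be confirmed falsely, or that the indirect effects will be biased upward.

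The award ended with 103 enrolled, about 26 per arm (103/4 = 25.75). In the baseline-PrEP setting at that size, false declarations fall to 3% to 12% because power is low, but the bias stays at 1.3 to 5.0 points. The primary Aim 1 comparison is unaffected.

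**What to change.** In the Aim 2 text of the Data Analysis by Aim section, state that every mediator model and every outcome model will include the baseline score of that mediator and baseline PrEP status (survey and DBS), regardless of arm balance or missingness. Add one sentence saying that the natural indirect effects assume no further mediator-outcome confounding given these covariates. Since baseline PrEP status then serves as a covariate, the baseline visit should not also count as an outcome occasion in these models.

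Both variables are already collected, so the cost is wording and a few model degrees of freedom. A longer list of common causes, and a sensitivity analysis for unmeasured confounding, can be left to the analysis plan.
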